## Abstract

**Background:**

Cerebral palsy (CP) is the most common physical disability of childhood, affecting movement and posture, resulting from a neurological insult during pregnancy or the neonatal period. While the brain lesion is static, the musculoskeletal sequelae in CP are often progressive and lifelong, associated with pain and can impact the lives of children with CP, their families and the healthcare system. The Australasian Cerebral Palsy Musculoskeletal Health Network (AusCP MSK) study will conduct comprehensive, population-based surveillance of children with moderate to severe functional mobility limitations (Gross Motor Function Classification System (GMFCS) levels III–V) to explore the early biomarkers of, and interactions between, musculoskeletal complications related to CP, including hip displacement, scoliosis and skeletal fragility.

**Methods:**

The AusCP MSK study involves three cohorts of children. Cohort A (n=500) is a multicentre retrospective (3 years) and prospective (4 years) cohort study in children aged 4–9 years that will be implemented at five sites across Australia and New Zealand. Retrospective data will include clinical history, information on CP diagnosis and other investigations (previous X-rays and biochemistry). Primary prospective outcomes will involve measures of hip displacement (migration percentage, acetabular index, femoral head orientation, Hilgenreiner’s epiphyseal angle), scoliosis (Anteroposterior/Posteroanterior and lateral spine X-ray), skeletal fragility (Dual Energy X-ray Absorptiometry, peripheral quantitative computed tomography), motor function (GMFCS, Manual Ability Classification System (MACS) and Communication Function Classification System (CFCS)) and range of movement (lower limb and spine). Cohort B (n=4000) is a retrospective analysis of data to evaluate fractures in children up to 18 years of age with CP (GMFCS I–V) from the New South Wales (NSW)/Australian Capital Territory CP Registers linked with corresponding records from NSW administrative health data (n=3000), and a New Zealand cohort of linked data from the New Zealand Cerebral Palsy Register to the Accident Compensation Corporation data for fracture claims (n=1000). Cohort C (n=30) will cross-sectionally examine bone quality through a transiliac bone biopsy in children undergoing scheduled hip surgery. Relationships between early biomarkers, early brain structure and musculoskeletal complications will be explored using multilevel mixed-effect models.

**Ethics and dissemination:**

Ethical approval for this study was granted by Children’s Health Queensland Hospital and Health Service Human Research Ethics Committee, The University of Queensland Human Research Ethics Committee and the New Zealand Health and Disability Ethics Committee.

Research outcomes will be disseminated via scientific conferences and publications in peer-reviewed journals; to the National Bodies and Clinicians; and to people with CP and their families.

**Trial registration number:**

Australian New Zealand Clinical Trials Registry number: ACTRN12622000788774p

STRENGTHS AND LIMITATIONS OF THIS STUDYThe study employs a prospective cohort design, allowing for the longitudinal assessment of musculoskeletal complications in children with moderate to severe cerebral palsy (CP).The study leverages multisource data linkage and imaging-based assessments across Australia and New Zealand enhancing population representativeness and generalisability.Possible risk of participant dropout and incomplete data across the study.Findings will be limited to children with moderate to severe CP (Gross Motor Function Classification System III–V) and results may not be generalisable to those with milder motor impairments.

## Introduction

 Cerebral palsy (CP) is the most common physical disability of childhood impacting 1 in 700 children in Australia.^1^ The condition affects the development of movement and posture, causing activity limitations, commonly attributed to non-progressive disturbances that occurred in the developing fetal or neonatal brain.^2^ The musculoskeletal sequelae in CP are progressive and life-long, extensively impacting the lives of children with CP, their families and the healthcare system and are often associated with significant pain.^3^

### Background to Musculoskeletal Abnormalities in Cerebral Palsy

The mechanical properties of bone size, shape and strength,^4 5^ are determined by genetics, bone growth and the forces applied to the bone by muscles and weightbearing.^6^ In children with CP, the initial static neurological insult leads to spasticity/dystonia and/or weakness, resulting in abnormal muscle forces on the developing skeleton, which impacts bone morphology and contributes to progressive hip displacement, scoliosis and skeletal fragility.^7^ These musculoskeletal alterations continue across the lifespan,^8^ contributing to reduced motor function, joint displacement (eg, hip displacement), increased joint pain, reduced habitual physical activity (HPA), increased sedentary behaviour, increased difficulty in care giving^9^ and decreased quality of life (QoL).^10^ The altered musculoskeletal development begins early in children with CP,^11^ resulting in muscles with reduced volume,^8 12^ with muscle fascicles that are stiffer,^13^ have reduced force production capacity,^11^ are thinner^14^ and shorter with longer tendons.^14 15^ The altered muscle activation patterns and reductions in muscle force, applied in abnormal directions, result in ongoing perturbations to skeletal development. In the hip, abnormal femoral head and acetabular development and coxa valga, all contribute to hip displacement.^16^ Increased hip adductor spasticity has also been considered as a contributing factor of hip displacement.^17^,^19^ At the spine, there is abnormal vertebral growth and reduced vertebral strength, which may contribute to scoliosis development.^20^ Reduced muscle force can also impact bone mass accrual throughout the skeleton, increasing the risk of fragility fracture.^21^ The precise age of onset of musculoskeletal complications, detailed knowledge of genetic predisposition, potential early biomarkers and complex interactions between the musculoskeletal complications of CP remain unclear.

### Hip displacement

Children with CP with moderate to severe mobility limitations (GMFCS levels III–V)^22^ have a high risk of progressive hip displacement with an incidence of approximately 35%.^23 24^ The pathophysiology of hip displacement in CP has been historically based on the spastic muscle model, which postulates that initial brain damage leads to spasticity characterised by muscle stiffness in the hip adductors and flexors, which pulls the femoral head out of the hip joint.^16^ While the spastic muscle model seems logical, there is evidence that hip displacement is unrelated to motor type, that is, there is no greater risk of hip displacement in children with spasticity than hypotonia.^23 24^ A more holistic model of hip displacement focuses on the negative features of CP as an upper motor neuron syndrome, with muscle weakness and limited weight bearing and walking function as causes of hip displacement.^16^ Hip abductor weakness and limited weight bearing/walking lead to abnormal joint forces, causing changes in the proximal femoral geometry (increased femoral neck anteversion and neck shaft angle) subsequently leading to hip displacement.^16 25^ When not treated early or effectively, displacement can lead to painful dislocation of the hip, with decreased function, increased carer burden and decreased QoL.^26 27^ A Victorian population-based study (n=323) recognised GMFCS as the strongest predictor of progression of hip displacement, defined as migration percentage (MP) on anteroposterior pelvic X-ray of greater than 30%, with increasing risk in children who are marginal ambulators GMFCS level III (41.3%); those non-ambulant but able to sit GMFCS IV (69%) and those unable to sit GMFCS V (90%).^24^ Based on the findings of these studies, a number of clinical guidelines for the systematic routine surveillance of hip displacement have been developed, including in Australia.^28^,^30^

Several longitudinal studies have demonstrated the effectiveness of population-based hip surveillance programmes on reduced rates of complete hip dislocation through early identification and timely referral for orthopaedic assessment and surgical management^31^,^33^; these do not, however, elucidate whether specific factors are protective against the development of progressive hip displacement for some children, such as increased habitual activity levels in children at GMFCS III, or floor mobility and standing function in those functioning at GMFCS IV.

There is no uniformly recognised treatment for prevention of hip displacement in children with CP, with interventions such as intramuscular Botulinum toxin A injections, Intrathecal Baclofen (ITB) and Selective Dorsal Rhizotomy (SDR) having limited effectiveness.^34^,^38^ Hip surgery (femoral osteotomy) is a well-recognised treatment for children with significant displacement or dislocation of the hips.^39^ Children with a hip MP of ≥30% are at higher risk of progressive hip displacement,^40^ and a hip with an MP ≥50% is at higher risk of dislocation.^41^ Surgical reconstruction has been demonstrated to be effective in improving pain and mobility in children with CP with marked hip displacement.^42^,^46^

### Scoliosis

Progressive spinal deformities, including scoliosis and kyphosis, are a major problem in children functioning at GMFCS levels IV and V, and can result in limitations to function and activity, cause pain and can be life-limiting due to respiratory compromise.^47^ Scoliosis is defined as a spinal curve of angle >10° as measured using the Cobb method.^48 49^ Similar to hip dysplasia, the incidence of scoliosis in children with CP has a direct correlation with GMFCS level.^50 51^ A Swedish prospective longitudinal study (n=1025), conducted within the follow-up healthcare programme and registry for children with CP (CPUP), reported the risk of severe scoliosis (Cobb angle >40°) at 10 years old was 2% for GMFCS III, 5% in GMFCS IV and 20% in GMFCS V. At 20 years, the prevalence of severe scoliosis (Cobb angle >40°) was 8% for GMFCS III, 35% for GMFCS IV and 75% for GMFCS V.^50^

Similarly, in an Australian cohort (n=292), a scoliosis (Cobb angle >10°) was found in 41% of individuals with CP and was directly related to increasing GMFCS level. Severe scoliosis (Cobb angle >40°) was most common in children functioning at GMFCS IV and V (18% and 48%, respectively). Curves were also more common in young people with more severe limitations in fine motor function and the presence of dystonia or mixed movement disorders.^52^ There is limited research that has explored protective factors for preventing scoliosis in children with CP. In addition, the relationship between hip displacement and scoliosis and the inter-related musculoskeletal complications are not well established in child populations.^49^ In adult populations with CP, the association between asymmetrical limited hip flexion (<90°), pelvic obliquity and clinical assessment of scoliosis is well established.^53^ In children with CP, postural asymmetry may play a role in increasing the likelihood of developing scoliosis, windswept and contracted hips.^54^ While the convexity of scoliosis has been associated with the high side of pelvic obliquity in young people with CP,^55^ not all who have a scoliosis and pelvic obliquity will develop significant hip displacement, and the natural history and aetiological mechanisms which underpin severe scoliosis in young people with CP are not clear. These studies highlight associations between hip abnormalities and scoliosis in children and adults with CP, however a causative relationship remains unclear. There are few prospective studies in children with CP that have investigated the early biomarkers of progression and the inter-relationship between hip displacement and scoliosis, confirmed by radiology, within the same cohort. Also, while guidelines for hip surveillance have been available in Australia since 2008,^29^ there is currently no national clinical guideline for the routine identification and surveillance of scoliosis.

To manage scoliosis, surgical intervention is considered the main treatment pathway,^56^ with non-surgical management including bracing and postural support in seating for prevention and slowing progression of minor curves. Bracing can improve sitting posture and trunk support, enabling better head, neck and upper limb control;^57 58^ however, bracing treatment can be difficult to prescribe and is poorly tolerated by young people with CP with significant dystonia or hypertonia, cognitive impairment or associated neurodiverse conditions due to the invasive and restrictive nature of casting and braces. Evidence of the effectiveness of bracing is mixed, with some demonstrating that bracing can slow curve progression, specifically in younger children with Cobb angles of less than 40°. ^57^,^59^ Other research, however, has suggested that for most children with CP braces are insufficient to reduce the requirement of surgical intervention,^58^ although in non-ambulatory individuals with scoliosis, optimising seating position has been identified as effective in increasing support and improving functional outcomes.^60^

### Skeletal fragility

Skeletal fragility is a significant complication of CP that worsens with disability and age.^61^ Skeletal fractures cause pain and result in diminished QoL and substantially increase costs of medical care as they can occur frequently and throughout the life span.^62^,^64^ Abnormal bone development during growth in children with CP increases the risk of pathological fracture that persists into adult life.^65^ The incidence of pathological fracture of the femur, tibia and humerus in children with CP is approximately 40%, with an annual fracture rate of 7%–10%.^66^ This has not, however, been evaluated in an Australian cohort. Although the overall incidence of fracture in children with CP is no greater than typically developing children (TDC), it is the mechanism of fracture (minimal or no trauma in children with CP), the fracture site (femur, tibia and humerus in CP as opposed to distal radius and ulna in TDC) and the associated morbidity that makes skeletal fragility a significant issue.^67^ The aetiology of reduced bone mass for age and reduced bone strength in children with CP is multifactorial. The primary factor is reduced mobility and associated reduced muscle force on bone.^66 68^ Other factors that can impact bone mass accrual include vitamin D deficiency, dietary calcium deficiency, undernutrition and low body weight, pubertal delay, and medications such as anticonvulsants, steroids and diuretics.^69 70^ Although Australian investigators have published consensus guidelines^71^ and undertaken studies on the prevention and treatment of skeletal fragility in children with CP,^72 73^ there is currently no predictive model to determine prognosis, best therapeutic actions or strategies to reduce the burden of fracture in children with CP.^74 75^ Improving our understanding of bone health would enable timely intervention to optimise bone strength, prevent complications of pain, pathological fracture and failure of orthopaedic devices. An important component of the AusCP Musculoskeletal Health Network (AusCP MSK) study is fully characterising the bone of children with CP through a combination of dual-energy X-ray absorptiometry (DXA), an *in vivo* peripheral quantitative CT (pQCT) and *ex vivo* bone mineral density distribution (BMDD).

Interventions designed to reduce skeletal fragility in children with CP include weight-bearing exercise, specifically including high ground reaction force or pull/strain on the skeleton over a prolonged period of time, such as vibration platforms.^76^ Positive treatment effects have been documented for weekly callisthenics programme^77^ and whole body vibration therapy.^78^ Current guidelines in CP recommend the treatment of fragility fractures with bisphosphonates.^71 73^ There is some contention, however, about the paucity of rigorous studies that examine the efficacy and safety of this approach.^72^

### Significance of the current study

The overarching goal of the AusCP MSK Network is to conduct comprehensive, population-based surveillance of children with CP to better understand the aetiology, age at onset, rate of progression and the clinical significance of musculoskeletal complications in CP as well as to identify therapeutic targets to inform prevention programmes for musculoskeletal complications. Musculoskeletal complications related to CP for non-ambulant children, including hip displacement, scoliosis and skeletal fragility are often severe and progressive, with a life-long impact. Currently in Australia, there are a number of guidelines in place to inform clinical practice in people with CP. These include the Australasian Cerebral Palsy Clinical Trials Network (Aus-CP-CTN) on early detection,^79^ early intervention^80^ and efficacy of interventions to improve functional outcomes.^81^ The Australian Hip Surveillance Guidelines for Children with Cerebral Palsy^28^,^30^ have been implemented to varying degrees in most states, however, there are no existing clinical guidelines or registries for spinal surveillance and skeletal fragility which this study aims to address. This has prevented the investigation of early biomarkers for, and the inter-relationship between, hip displacement, scoliosis and skeletal fragility. These knowledge gaps have hampered the development of timely and effective interventions aimed at either preventing or mitigating these musculoskeletal complications. Ultimately, early detection of musculoskeletal complications in children with CP, coupled with evidence-based preventative interventions, will reduce the impact of spine, hip and skeletal fragility disorders in children, adolescents and adults with CP. This will support people with CP to have the best possible musculoskeletal health, physical function and QoL, leading to a reduction in healthcare-related and societal costs. The AusCP MSK—MRF2015970 is prospectively registered at ACTRN: ACTRN12622000788774p and ACTRN12622000782730p.

## Methods and analysis

### Aims and hypotheses

The AusCP MSK primary study objective is to:

Identify early biomarkers of onset/progression of musculoskeletal complications (hip displacement, scoliosis, fragility fracture) that predict the severity and rate of progression of musculoskeletal complications (MP>30%, Cobb angle>10°, lateral distal femur (LDF) bone mineral density (BMD) Z-score< −2.0) at 8–13 years, leading to natural history data that can be used to inform early intervention clinical trials and identify new therapeutic targets.

The AusCP MSK secondary study objectives are to:

Identify the relationship between early brain structure (clinical MRIs), aetiology of CP and musculoskeletal development at 1–4 years of age on disability outcomes at 8–13 years of age.Determine the costs and consequences of medical and allied health resource use (HRU), and poor QoL at 8–13 years of age, related to severity of musculoskeletal complications at 4–9 years of age.Determine prevalence, HRU costs and clinical characteristics of children and adolescents with CP who sustain a pathological fracture, evaluate complementary data for CP patient bone quality and develop a predictive model for fracture.

These aims will be explored through the following hypotheses:

Higher prevalence of musculoskeletal risk factors for hip displacement, scoliosis, reduced BMD for age, such as Gross Motor Function Measure (GMFM), HPA/sedentary behaviour, nutritional status, body composition (fat mass/fat free mass on DXA), at 4–9 years of age will lead to poorer musculoskeletal outcomes at 8–13 years of age.The location and extent of the brain lesion(s) on structural MRI, pathophysiology of CP (motor type and distribution), motor capacity (GMFM-88) at 4–9 years of age will predict severity of musculoskeletal complications (hip displacement, scoliosis, bone fragility) and performance outcomes (Pediatric Evaluation of Disability Inventory, Computer Adapted Test, PEDI-CAT) at 8–13 years of age.The location, extent of the brain lesion(s) on semiquantitative MRI (<6 years) will predict the severity of musculoskeletal outcomes (MP>30%, Cobb>10°), at 8–13 years of age.Healthcare costs will be higher for children with greater adverse musculoskeletal biomarkers at 4–9 years of age and will lead to poorer outcomes and QoL (consequences) at 8–13 years of age.Pathologic fracture will be a major health burden in children with CP that increases with GMFCS and age.The identification of children with CP at greatest risk of fracture through a predictive tool will enable the determination of prognosis, inform therapeutic action and reduce fracture burden.Bone quality of children with moderate-to-severe CP will be abnormal compared with TDC;Genetic variation will influence onset and progression of musculoskeletal complications in CP.

### Study design

The AusCP MSK is a multicentre prospective (4 years) and retrospective (3 years) cohort study that will be implemented nationally and internationally at five sites: (1) Queensland Children’s Hospital (QCH); (2) Royal Children’s Hospital, Melbourne (RCH); (3) The Children’s Hospital at Westmead (CHW); (4) The Sydney Children’s Hospital (SCH) and (5) The Starship Children’s Hospital (SCH), New Zealand. This study builds on the foundations of previous studies by the research team: epidemiology of CP, early diagnosis of CP and early surveillance of CP and will undertake further comprehensive surveillance in three cohorts (A, B and C) of children with CP, outlined in figure 1. The study commenced in February 2024 and will be completed by 29 February 2028.

**Figure 1 F1:**
[figure not shown]
Visual description of the AusCP MSK study cohorts A, B and C. ACC, Accident Compensation Corporation; ACT, Australian Capital Territory; CHW, The Children’s Hospital at Westmead; CP, cerebral palsy; ED, emergency department; GMFCS, Gross Motor Function Classification System; NSW, New South Wales; QCH, Queensland Children’s Hospital; RCH, The Royal Children’s Hospital; SCH (NZ), Starship Children’s Hospital New Zealand.

*Cohort A* (n=500) involves the collection of 3-year retrospective data and subsequent 4-year prospective follow-up (baseline (T1) and three annual assessments (T2, T3 and T4)) for a range of musculoskeletal measures with children with CP GMFCS III–V, capturing development from ages 4 to 13 years, providing 7 years of data. This approach enables the identification of early biomarkers of musculoskeletal change, acknowledging that while prospective tracking begins at age 4, important features of musculoskeletal health before this age can be explored through retrospective data collection. *Cohort B* focuses on a retrospective analysis of data from individual’s records from both Australian and New Zealand cohorts to identify clinical presentations for fractures among children with CP GMFCS I–V, aged less than 18 years of age from 2001. The Australian cohort (n~3000) will be retrieved from the NSW/Australian Capital Territory (ACT) CP Register that has been linked with admitted hospital, emergency department and outpatient data collections. The New Zealand cohort (n=~1000) will involve extracting clinical data from the New Zealand Cerebral Palsy Register and linking it to deidentified fracture claims data in the Accident Compensation Corporation database. *Cohort C* includes a single-timepoint examination of bone quality, quantity and turnover in up to 30 children with CP, GMFCS III–V, undergoing scheduled hip surgery at QCH with an exposed iliac crest. A transiliac bone biopsy will be performed using a 5 mm to 7.5 mm diameter trephine. This biopsy will be subjected to testing of histomorphometry and quantitative backscatter electron microscopy imaging (qBEI) for the analysis of: (1) bone cellular activity and (2) BMDD.^82^

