### Eligibility criteria

#### Australian sample

Participants are eligible to be included in the prospective studies (cohort A and C) if the following criteria apply: (1) have a diagnosis of CP and gross motor function classified at GMFCS levels III–V; (2) aged between 4.00 and 9.99 years of age at the time of recruitment (any age less than 18.00 years for cohort C); (3) have a parent or legal guardian that is capable of giving signed, informed consent.

Participants will be excluded if the parent/legal guardians’ English language skills are not sufficient to understand the study information, provide informed consent and/or complete the parent-reported study questionnaires.

For study B (cohort B), data extracted from the NSW/ACT CPR will allow records for individuals with CP (GMFCS I–V), aged less than 18 years to be matched in data linkage. The CPR is a population-based database registry with multiple ascertainment strategies of individuals with CP who were born or live in NSW or ACT.

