#### New Zealand sample

Participants are eligible to be included in the prospective studies (cohort A) if the following criteria apply: (1) have a diagnosis of CP and gross motor function classified at GMFCS levels III–V; (2) aged between 4.00 and 9.99 years of age at the time of recruitment. For study B (cohort B), data extracted from the New Zealand Cerebral Palsy Register will be linked to fracture claims data in the Accident Compensation Corporation database for children with CP (GMFCS I–V) aged less than 18 years.

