##### Outcomes

For cohort groups (A, B and C) the following *retrospective early life data* will be collected at one timepoint only (baseline, T1):

I. Where available, clinical history will be retrieved from medical records, participating registries, clinical trial and neonatal discharge summaries including: sex, ethnicity, gestational age at birth, birth weight, delivery, singleton or one of multiple births, perinatal risk factors (genetic history, infection) and MRI brain findings.

II. Age and severity of CP information will include: age at CP diagnosis, GMFCS,^83^ Manual Ability Classification System (MACS),^84^ Communication Function Classification System (CFCS)^85^ and the Eating and Drinking Assessment Classification System (EDACS).^86^

III. Parent-reported early intensive therapy interventions will include: (1) age at commencement (2), the frequency and duration (dose) and (3) mode (cohort A, C)

IV. Investigations will include: X-rays of hip and/or spine, biochemistry including 25-hydroxy vitamin D (250HD) and alkaline phosphatase (cohort A, C).

Prospective longitudinal study outcomes for cohort A and C, except for DXA scans, will be measured at baseline (T1, year 1), 12 months postbaseline (T2, year 2), 2 years postbaseline (T3, year 3) and 3 years postbaseline (T4, year 4). The AusCP MSK schedule of assessments for all cohort studies (A, B, C) is outlined in table 1.

**Table 1 T1:** Data pooling plan for AusCP MSK studies

Retrospective study cohort A at 1–5 years/cohort B at fracture			Prospective follow-up from 4 to 9 yearsCohorts A and C		
Domain/test	**A**	**B**	TEST	**A**	**C**

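### Cohort A's retrospective window is defined in three ways that do not agree; if the 3-year look-back governs, about a third to a half of children have no musculoskeletal data at 1–4 years for secondary objective 1

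*Protocol article*

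**What the plan says.** All references are to the protocol article.

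- **Study design:** Cohort A "involves the collection of 3-year retrospective data and subsequent 4-year prospective follow-up". The same paragraph adds the two parts to 7 years of data and says that features of musculoskeletal health before age 4 can be studied through the retrospective part. The abstract also gives 3 retrospective and 4 prospective years.
- **Eligibility criteria:** Australian children in Cohort A are "aged between 4.00 and 9.99 years of age at the time of recruitment". The New Zealand sample has the same range.
- **Aims and hypotheses:** secondary objective 1 relates early brain structure, aetiology and "musculoskeletal development at 1–4 years of age on disability outcomes at 8–13 years of age".
- **Table 1 (Outcomes):** the column header reads "Retrospective study cohort A at 1–5 years/cohort B at fracture". Hip displacement, scoliosis and range of motion are ticked for Cohort A in that column.
- **Outcomes, text before Table 1:** retrospective early-life data "will be collected at one timepoint only (baseline, T1"). They include perinatal history, earlier hip or spine X-rays and biochemistry, with no look-back limit stated. The last prospective visit, T4, is 3 years after baseline.
- **Secondary outcomes:** brain MRI may come from any age.

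**The concern.** One definition of the retrospective period counts back in calendar time from T1. The other two are fixed by the child's age. They agree only for a child recruited at about 4. For a child recruited at 9, reaching back to age 1 takes 8 years, so a 3-year look-back cannot deliver the Table 1 band or the exposure named in the objective.

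Early musculoskeletal development is one of the three exposures in secondary objective 1. Under a 3-year look-back, whether a child has it is decided by age at recruitment. That age also fixes how old the child is at the last outcome visit. The resulting gap comes from the design; it is not ordinary missing data.

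The retrospective data are collected once per child and the study has been under way since February 2024. Sites that read the rule differently would retrieve different records.

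**Working it through.** **Inputs.** Look-back 3 years (Study design); recruitment age *a* from 4.00 to 9.99, a range of 5.99 years (Eligibility criteria); exposure age 1–4 years (Aims and hypotheses); Table 1 band 1–5 years; T4 = T1 + 3 years (Outcomes); 500 enrolled, 90% with 4 years of data (Sample size).

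**The plan's own figures.** 3 retrospective years + 4 annual assessments = 7, as stated. 0.90 × 500 = 450, as stated. The article gives no figure for the number of children with data at 1–4 years.

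**Look-back interval.** Read as the 3 years before T1, it is [*a* − 3, *a*]:

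| Recruited at | Look-back covers ages |
|---|---|
| 4.00 | 1.00–4.00 |
| 7.00 | 4.00–7.00 |
| 9.99 | 6.99–9.99 |

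There is time before age *u* only if *a* − 3 < *u*. For *u* = 4.00 (band ends at the 4th birthday) this needs *a* < 7.00. For *u* = 5.00 (age 4 included) it needs *a* < 8.00.

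**Share with no look-back time in the band.** The article gives no age distribution, so uniform ages are assumed first. The skewed cases use a linear density weighted 2:1 towards the younger or the older end.

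| Recruitment ages | Band to 4.00 | Band to 5.00 |
|---|---|---|
| Uniform | 2.99/5.99 = 49.9% (about 250 of 500) | 1.99/5.99 = 33.2% (about 166 of 500) |
| Skewed young | 41.6% | 25.8% |
| Skewed old | 58.2% | 40.6% |

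With uniform ages the remaining children have partial cover. Averaged over all recruits it is about 0.75 of 3 years (25%), or 1.25 of 4 years (31%).

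**Link with outcome age.** Age at T4 is *a* + 3. Children with time before 4.00 (*a* < 7.00) are all under 10 at T4, and children without it are all 10 or older. With age 4 included, the dividing age at T4 is 11.

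**Children with both exposure and an outcome at 8 or older.** *a* + 3 ≥ 8 needs *a* ≥ 5.00, so recruits under 5.00 drop out (1.00/5.99 = about 17%). What remains, with uniform ages:
- Band to 4.00: recruited 5.00–6.99, 2.00/5.99 = 33.4%, about 167 of 500.
- Band to 5.00: recruited 5.00–7.99, 3.00/5.99 = 50.1%, about 250 of 500.

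If the planned 90% retention applied equally at all ages, these would be 0.90 × 167 ≈ 150 and 0.90 × 250 = 225. The only child with the whole band to 4.00 is one recruited at 4.00, who is 7.00 at T4.

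**If Table 1 or the unlimited record retrieval in the Outcomes text governs,** the window excludes no one.

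**The case against.** The strongest reply is that the strict calendar reading is inferred. No sentence limits all retrospective data to the 3 years immediately before T1. Ages 1 to 4 are themselves a 3-year span, Table 1 is set by age, and the early-life records carry no limit. Since every recruit is at least 4.00, no birth or neonatal item could fall inside a 3-year look-back, so that limit cannot govern everything collected. Figure 1, which could not be consulted here, may settle the matter. This stands as a reason not to treat the look-back as the established design. It does not remove the conflict: the prospective years are described as following the 3-year period and the two are summed to 7 years, which reads naturally as one continuous span per child. These are stated design elements, so this is not detail left to a fuller document.

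A reader might infer that secondary objective 1 cannot be answered. The documents do not support that. Brain structure and aetiology do not depend on the window, none of the listed hypotheses uses musculoskeletal status at 1–4 years as a predictor, and even under the look-back half to two-thirds of children (uniform ages) have some early data.

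A reader might also infer that a child recruited at 9 contributes nothing from before age 6. That holds only for look-back data under the 3-year reading. Nor is the remark about features before age 4 false: it describes the cohort and does not promise data for each child.

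**Conclusion.** The point holds as an inconsistency in the definition of the retrospective window, with a conditional consequence. The 3-year period, the 1–5-year band and the 1–4-year exposure cannot all apply to children recruited at 4.00–9.99 years, and the article does not rank them.

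If the 3-year look-back governs, about half of Cohort A lacks any musculoskeletal look-back before age 4.00, or about a third if age 4 is included. These fractions rest on uniform recruitment ages; the skewed cases tried give about 26–58%. If an age-based rule governs, the window itself causes no loss. The consequence is confined to the musculoskeletal-development part of secondary objective 1. There, availability of the exposure would be tied to outcome age, with no early data for children whose outcomes fall in the upper part of the 8–13 band.

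**What to change.** State one retrospective rule, defined by age, and use it in the abstract, Study design, Aims and Table 1. For every Cohort A child, retrieve the available hip and spine X-rays, range-of-motion records and biochemistry from age 1 (or the first available record) to T1. Record the age at each and analyse early development on the age scale. State whether the exposure band ends at the 4th or the 5th birthday. This fits Table 1 and the record list in Outcomes.

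The cost is extra retrieval for older recruits and possibly a wording change in the consent or ethics look-back. Older records will be less complete, so completeness should be reported by age at recruitment. The rule does not help recruits under 5.00, who do not reach 8 by T4.

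If the 3-year window is kept, limit the 1–4-year musculoskeletal analysis to children with both exposure data and an outcome at 8 or older, and state that n: about 167 of 500 (recruited 5.00–6.99), or about 250 (recruited 5.00–7.99) if age 4 is included. Both assume uniform ages and are before attrition; replace them with the actual recruitment ages. Counting all recruits under 7.00, also about 250, would be wrong because it includes those too young to reach 8.
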